# Titanium versus absorbable tacks comparative study (TACS): a multicenter, non-inferiority prospective evaluation during laparoscopic repair of ventral and incisional hernia: study protocol for randomized controlled trial

**DOI:** 10.1186/s13063-015-0779-x

**Published:** 2015-06-04

**Keywords:** Ventral/incisional hernia repair, Laparoscopy, Lightweight polypropylene mesh, Absorbable tacks, Titanium helicoidal tacks, Hernia

## Abstract

**Background:**

Laparoscopic repair of ventral and incisional hernias has gained popularity since many studies have reported encouraging results in terms of outcomee and recurrence. Choice of mesh and fixation methods are considered crucial issues in preventing recurrences and complications. Lightweight meshes are considered the first choice due to their biomechanical properties and the ability to integrate into the abdominal wall. Titanium helicoidal tacks still represent the “gold standard” for mesh fixation, even if they have been suggested to be involved in the genesis of post-operative pain and complications. Recently, absorbable tacks have been introduced, under the hypothesis that there will be no need to maintain a permanent fixation device after mesh integration. Nevertheless, there is no evidence that absorbable tacks may guarantee the same results as titanium tacks in terms of strength of fixation and recurrence rates. The primary end point of the present trial is to test the hypothesis that absorbable tacks are non-inferior to titanium tacks in laparoscopic incisional and ventral hernia repair (LIVHR) by lightweight polypropylene mesh, in terms of recurrence rates at 3-year follow-up. Surgical complications, post-operative stay, comfort and pain are secondary end points to be assessed.

**Methods/Design:**

Two hundred and twenty patients with ventral hernia will be randomized into 2 groups:

Group A (110) patients will be submitted to LIVHR by lightweight polypropylene mesh fixed by titanium tacks;

Group B (110) patients will be submitted to LIVHR by lightweight polypropylene mesh fixed by absorbable tacks.

**Discussion:**

A few retrospective studies have reported similar results when comparing absorbable versus non-absorbable tacks in terms of intraoperative and early post-operative outcomes. These studies have the pitfalls to be retrospective evaluation of small series of patients, and the reported results still need to be validated by larger series and prospective studies.

The aim of the present trial is to investigate and test the non-inferiority of absorbable versus non-absorbable tacks in terms of hernia recurrence rates, in order to assess whether the use of absorbable tacks may achieve the same results as non-absorbable tacks in mid-term and long-term settings.

**Trial registration number:**

NCT02076984: 5 June 2014 (ClinicalTrials.gov)

**Electronic supplementary material:**

The online version of this article (doi:10.1186/s13063-015-0779-x) contains supplementary material, which is available to authorized users.

## Background

During the past 50 years, incisional and ventral hernia repair surgery has evolved from direct suture repair to the use of synthetic mesh to obtain a tension-free repair [1–3]. Finally, the tension-free concepts have been applied to laparoscopic surgery. Laparoscopic repair of incisional/ventral hernias (LIVHR) has gained increasing popularity, since many studies, included three meta-analyses, have reported encouraging results in terms of wound infection, hospital stay and post-operative pain, and recurrence rates comparable with the open approach [1–8].

Besides patient selection (age, sex, comorbidities, obesity, hernia site and size, eventual recurrence and type of previous abdominal surgery) and patient compliance, the choice of the mesh (bio-materials, size and shape) and fixation methods (titanium tacks, absorbable tacks, fibrin glue) are considered crucial issues to achieve optimal results and reduce complication and recurrence rates [4,5,9–12]. Lightweight meshes are often considered the first choice for hernia repair by many authors, since the evidence that the decreased density of the non-absorbable material could reduce the “foreign-body response,” improve abdominal wall compliance, cause less shrinkage and enhance the integration in host tissues [13–15]. Titanium helicoidal tacks are still considered the “gold standard” for mesh fixation [16–20]. However, several complications caused by these tacks have been reported (adhesion formation and bowel perforation). Furthermore, these devices may be involved in the genesis of some post-operative pain. Recently, absorbable tacks have been introduced [21] in combination with lightweight meshes, under the assumption that permanent fixation is no longer needed after the mesh is integrated within host tissues, potentially avoiding some of the above-described tack-related complications. Nevertheless, the efficacy of the use of absorbable tacks has never been compared to titanium tacks in a prospective analysis: only a few observational studies report similar results during a mid-term post-operative follow-up [21–23].

The Italian Society of Endoscopic Surgery recently carried out a Consensus Conference with a systematic literature search on this topic and concluded that “*mesh fixation with spiral tacks should be considered the standard method of fixation in laparoscopic ventral/incisional hernia repair*” and that “*there is not enough evidence to make any recommendation in favor or against the use of the absorbable fixing devices*” [24]. Also, the International Endohernia Society published its evidence-based guidelines and came to similar conclusions. Both guideline panels found very little literature about the role of absorbable fixing devices and stressed the need for further research about it [25]. In fact, the current evidence on the use, safety and efficacy of absorbable tacks for mesh fixation is still based on few retrospective studies giving inconclusive results [21,22], and a recent report from a National Register [26], which concludes that the use of absorbable tacks is related to an increased risk of hernia recurrence. The latter deals with a very large number of patients but does not provide any information either about the type of mesh or the specific kind of tacks used. The absence of this crucial information limits the usefulness of the study. The direct comparison of absorbable tacks with the current “gold standard,” represented by titanium tacks appears to be the best way to assess their efficacy and safety.

Our study primary objective is to determine if absorbable tacks are non-inferior to titanium tacks for lightweight mesh fixation during LIVHR in the end point of recurrence rate, considering a follow-up of 3 years.

The secondary objectives are to evaluate the possible superiority of the absorbable tacks in improving post-operative stay, complications, pain and comfort.

Our choice of a non-inferiority trial design was based on the assumption that some of the complications related to the use of metal spiral tack could be avoided by the use of absorbable devices if their non-inferiority to the reference treatment (metal tacks) is demonstrated.

This protocol has been prepared in accordance with Standard Protocol Items: Recommendations for Interventional Trials (SPIRIT) [27] and the Consolidated Standards of Reporting Trials (CONSORT 2010) [28], taking into accounts its Extension for Nonpharmacologic Treatment Interventions [29] and the CONSORT Statement for Reporting Noninferiority and Equivalence Trials [30].

## Methods/Design

### Trial design, locations and organizational structure

The TACS trial is a multicentric prospective randomized study. It will involve five surgical units having extensive experience in both metallic and absorbable tacks for LIVHR (this means that each surgeon participating in the study usually performs more than fifty procedures per year with the devices used in the study).

The Reference Center (General Surgery Unit, ICOT Hospital, Latina, Italy) will coordinate the study and handle the data analysis and interim evaluations.

The study will develop according to the *Helsinki Declaration*. It obtained the Ethical Committee approval (Independent Ethical Committee “Lazio 2”) on 26 May 2014 prior to registration (reference number asl_lt/15675/A001/2014)*.*

### Study population and eligibility criteria

All consecutive patients referred to the involved surgical units will be checked to determine eligibility, by one dedicated team member, according to the inclusion and exclusion criteria specified in an additional file (see Additional file 1).

All the eligible patients will be consecutively enrolled in the study until the sample size of 220 patients is reached. The included patients will be divided into two groups:Group A: patients submitted to LIVHR by lightweight polypropylene mesh fixed by titanium helicoidal tacks (control group);Group B: patients submitted to LIVHR by lightweight polypropylene mesh fixed by absorbable tacks (study group).

Each patient will be introduced to the trial by a member of the research group and receive an explanation of the study protocol (including random assignment of the fixation device that will be used during surgery). A specific informed consent regarding participation in the trial, randomization and explanation of the laparoscopic hernia repair, with no disclosure about the fixation device will be obtained and signed before enrolling in the study.

### Randomization, allocation concealment, and blinding

A simple 1:1 allocation ratio randomization (without any restriction) will be guaranteed by an on-line computerized random generator. Patients will be randomly assigned to either Group A or Group B in the operating room, just before surgery.

Patients will be kept blind to the allocation status. Furthermore, post-operative controls will be performed at each center by a physician not directly involved in the study. He will be kept blind to the particular device used on each patient. Due to the nature of the intervention, the operating staff cannot be blinded to allocation but will be instructed not to disclose the allocation status of the participant at any time.

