### Intervention, preoperative and post-operative management

All patients will be assessed preoperatively by clinical examination and abdominal computed tomography (CT) or ultrasound (US) scan to evaluate the size and number of the defect(s).

The devices used in the study (meshes and tacks) will be:Physiomesh™ (Ethicon Endo-Surgery, Johnson & Johnson, Inc.), a lightweight polypropylene mesh with double face absorbable layer engineered to be placed on the peritoneal surfaceProtack™ (Covidien Surgical, Mansfield, MA, USA), permanent titanium helicoidal tacksSecurestrap™ (Ethicon Endo-Surgery, Johnson & Johnson, Inc.), “U”-shaped absorbable tacks made by polydioxanone, completely resorbed by hydrolysis within 12–18 months after implantation

All the procedures will be carried out using the same surgical technique, already described in previous studies [22,23]. In particular, there will be careful adhesiolysis of the entire abdominal wall, a search for additional defects, overlapping the defect for at least 3 cm on each side, setting the tacks at the distance of 1.5 cm in a double crown configuration [31] and no use of transfixed sutures or glue. After surgery, compressive dressing will be placed for 4 weeks.

Each surgeon will be provided with a precise description of the standardized technique and a checklist of the aforementioned necessary technical items to be controlled, filled for every patient and turned back to the Reference Center. Adherence to the protocol will be assessed by review of the procedure videos: all centers will share the videos with the Reference Center. The operations performed by the Reference Center will be examined by the primary surgeon of another participating center who will check that all items on the checklist have been correctly performed.

A member of the operating team will note the patients and intervention characteristics in an online database including the following parameters:Patient characteristics (sex, age, comorbidities, personal therapy)Hernia features (location and size)Mesh sizeType of tacks (absorbable/non-absorbable)Number of tacks usedOperating timePost-operative hospital stay

Post-operative complications during the index admission (according to the Clavien-Dindo classification) [32].

Acute post-operative pain (using the Visual Numeric Scale (VNS) for pain classification) [33].

Pain management (use of analgesic drugs).

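### Patients are randomized before surgery although the arms differ only in the tack, so unblinded surgeons can know the arm while choosing mesh size and overlap, and patients who end up without tacks are already allocated

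*Protocol article*

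**What the plan says.** The Protocol article, under *Randomization, allocation concealment, and blinding*, fixes the time of allocation: "Patients will be randomly assigned to either Group A or Group B in the operating room, just before surgery". An online generator gives simple 1:1 randomization. The same section says that "the operating staff cannot be blinded to allocation", although staff are told not to disclose the arm. Patients are blinded, and so is the physician who performs the follow-up checks: "He will be kept blind to the particular device used on each patient".

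Under *Intervention, preoperative and post-operative management*, both arms receive the same mesh and only the tack differs. The operative steps include "careful adhesiolysis of the entire abdominal wall, a search for additional defects, overlapping the defect for at least 3 cm on each side". The same sentence fixes the tack spacing at 1.5 cm in a double crown and excludes transfixed sutures and glue. The section also sets these safeguards:

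- "All the procedures will be carried out using the same surgical technique, already described in previous studies";
- "a checklist of the aforementioned necessary technical items to be controlled, filled for every patient" and returned to the Reference Center;
- "Adherence to the protocol will be assessed by review of the procedure videos";
- imaging of the size and number of defects before the operation;
- recording of hernia size, mesh size and number of tacks by a member of the operating team.

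**The concern.** The tack is used only once the mesh is in place. Allocating before the first incision therefore lets the arm be known during steps that do not depend on the arm but may affect recurrence, which is the primary end point. Two problems follow.

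- **Influence on the operation.** A surgeon who trusts one tack less can use a larger mesh or a wider overlap. The 3-year comparison would then mix the effect of the tack with the effect of that extra margin.
- **Patients who receive no tacks.** The *Study population and eligibility criteria* section describes each group by the tack that fixes the mesh. A patient whose operation ends without tack fixation fits neither description but has already been allocated. If kept, such patients shrink a real difference. If dropped, the decision follows events in an operation run by staff who can know the arm.

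In a non-inferiority trial, anything that makes the arms look more alike can produce a false success, so avoidable sources of this kind deserve attention.

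**Working it through.** **Inputs from the Protocol article, *Statistical methods*:** 110 per arm; reference recurrence 0.07; absorbable recurrence 0.13 under the null, so the margin is 0.13 − 0.07 = 0.06; one-sided unpooled Z test at 0.05; stated power 80%. **Assumed, because the document gives no figure:** the share *f* of each arm that receives no tacks, and any change in recurrence caused by surgeon behaviour.

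**Step 1. The plan's own figure.** With equal true rates of 7%, the number per arm is 2 × 0.07 × 0.93 × (1.645 + 0.842)² / 0.06² = 223.6, so 224. At 110 per arm, SE = √(0.1302/110) = 0.0344 and power is Φ(0.06/0.0344 − 1.645) = Φ(0.099) = 53.9%. The stated 80% is not reproduced under equal rates. That is a separate matter and nothing below depends on it.

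**Step 2. Dilution if untacked patients are analysed as randomized.** Put the true difference among tacked patients at the margin (7% v 13%) and give untacked patients 7% recurrence in both arms. The absorbable-arm rate is then p = 0.07*f* + 0.13(1 − *f*), and the observed difference is d = 0.06(1 − *f*). With SE = √{[0.07 × 0.93 + p(1 − p)]/110}, the chance of declaring non-inferiority is Φ((0.06 − d)/SE − 1.645).

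| *f* (assumed) | p | d (points) | SE | (0.06 − d)/SE | False non-inferiority |
|---|---|---|---|---|---|
| 0 | 0.1300 | 6.0 | 0.0402 | 0 | 5.0% |
| 2% | 0.1288 | 5.9 | 0.0401 | 0.030 | 5.3% |
| 5% | 0.1270 | 5.7 | 0.0400 | 0.075 | 5.8% |
| 10% | 0.1240 | 5.4 | 0.0397 | 0.151 | 6.8% |

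If untacked patients have 13% recurrence instead, the 10% row becomes 6.7% and the others barely move.

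**Step 3. The same patients excluded instead.** With 110(1 − *f*) per arm and equal 7% rates, power falls from 54% to 53%, 52% or 50% for *f* = 2%, 5% or 10%. This makes non-inferiority harder to show. Any selection bias from the exclusions has unknown sign.

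**Step 4. Surgeon influence, for illustration only.** Start again from 7% v 13%.

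- Extra care lowers recurrence in the absorbable arm by an assumed 1 point (7% v 12%): Φ(0.01/0.0394 − 1.645) = 8.2%.
- The same by 2 points (7% v 11%): Φ(0.02/0.0385 − 1.645) = 13.0%.
- Extra care lowers recurrence in the titanium arm by 1 point (6% v 13%): Φ(−0.01/0.0393 − 1.645) = 2.9%.

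The same behaviour raises or lowers the error according to the arm in which it occurs. The document gives no basis for choosing a size.

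**Step 5. What the safeguards leave open.** Fixed tack spacing and the exclusion of sutures and glue close the most direct ways to reinforce a distrusted tack. Mesh size and overlap stay open: every overlap of 3 cm or more passes the checklist and the video review. Imaging before surgery does not settle mesh size, because the plan also requires a search for additional defects during the operation. Mesh size is recorded, but not necessarily before allocation.

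**The case against.** The strongest case on the other side is that this is already a careful design. Allocation in the operating room from an online generator is late and protects concealment up to that point. The *Trial design, locations and organizational structure* section requires units with extensive experience of both tack types, and surgeons who usually do more than fifty procedures a year with the study devices, which weakens the idea that they distrust one of them. Technique is standardized, the checklist and videos are reviewed, and another center's surgeon examines the Reference Center's operations. An imbalance in mesh size relative to hernia size would show in the recorded data. Patients and follow-up physicians are blinded.

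Most of this stands, and it narrows the risk to overlap beyond 3 cm and other choices that the technique does not fix. It does not close the gap: generous and minimal overlaps both comply, video reviewers are not said to be blinded, and blinding at follow-up protects assessment of the outcome, not the operation.

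A reader might infer three stronger points that the document does not support.

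- *The timing favours non-inferiority.* The *Background* calls titanium the reference method and cites a register report of more recurrence with absorbable tacks, so compensation in the absorbable arm is conceivable. It is not documented, and the opposite is possible. Dilution has that sign only under analysis as randomized, and the article names no analysis population.
- *The surgeon is told the arm before the first incision.* The text gives the time of assignment, not of disclosure. Early knowledge is possible and unprevented, but not stated.
- *The article wrongly omits conversions and the analysis population.* A condensed article may leave these to the full protocol or analysis plan, and no defect is claimed there.

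**Conclusion.** The point holds as a modest weakness in a timing that the plan itself states; it is neither a contradiction nor an error. Because allocation precedes surgery, steps common to both arms can be influenced by knowledge of the arm, and patients who never receive tacks are already randomized. The safeguards reduce this without removing it.

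The bias can favour non-inferiority but has no fixed direction. The dilution part is small: at an assumed untacked share of 5% or less, it adds under 1 percentage point to the 5% error, and at 10% about 1.8 points. These figures rest on assumed shares that are equal in both arms, on the same recurrence in untacked patients of both arms, and on analysis as randomized. The part due to surgeon behaviour cannot be sized from the document. The change is worth making because it is cheap and removes both problems for future patients whichever analysis population is used.

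**What to change.** For patients not yet randomized, amend the sentence on timing so that allocation takes place *during the operation, after adhesiolysis, defect measurement and choice of mesh size are complete and recorded, immediately before mesh fixation*. Add that patients whose operation does not reach that point are logged as not randomized, and that patients already randomized stay in their allocated arm.

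The generator, sample size and test stay the same, and the consent process already explains random assignment of the device. The change needs the formal amendment and new ethical approval described under *Good clinical practice and ethical approval*. In the operating room it costs a short pause, with both devices at hand. Enrollment began on 1 June 2014, so the trial would contain two allocation timings. Results should therefore also be reported by allocation timing as a sensitivity analysis. The change cannot help patients randomized before it.

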### Intervention, preoperative and post-operative management

All patients will be assessed preoperatively by clinical examination and abdominal computed tomography (CT) or ultrasound (US) scan to evaluate the size and number of the defect(s).

The devices used in the study (meshes and tacks) will be:Physiomesh™ (Ethicon Endo-Surgery, Johnson & Johnson, Inc.), a lightweight polypropylene mesh with double face absorbable layer engineered to be placed on the peritoneal surfaceProtack™ (Covidien Surgical, Mansfield, MA, USA), permanent titanium helicoidal tacksSecurestrap™ (Ethicon Endo-Surgery, Johnson & Johnson, Inc.), “U”-shaped absorbable tacks made by polydioxanone, completely resorbed by hydrolysis within 12–18 months after implantation

All the procedures will be carried out using the same surgical technique, already described in previous studies [22,23]. In particular, there will be careful adhesiolysis of the entire abdominal wall, a search for additional defects, overlapping the defect for at least 3 cm on each side, setting the tacks at the distance of 1.5 cm in a double crown configuration [31] and no use of transfixed sutures or glue. After surgery, compressive dressing will be placed for 4 weeks.

Each surgeon will be provided with a precise description of the standardized technique and a checklist of the aforementioned necessary technical items to be controlled, filled for every patient and turned back to the Reference Center. Adherence to the protocol will be assessed by review of the procedure videos: all centers will share the videos with the Reference Center. The operations performed by the Reference Center will be examined by the primary surgeon of another participating center who will check that all items on the checklist have been correctly performed.

A member of the operating team will note the patients and intervention characteristics in an online database including the following parameters:Patient characteristics (sex, age, comorbidities, personal therapy)Hernia features (location and size)Mesh sizeType of tacks (absorbable/non-absorbable)Number of tacks usedOperating timePost-operative hospital stay

Post-operative complications during the index admission (according to the Clavien-Dindo classification) [32].

Acute post-operative pain (using the Visual Numeric Scale (VNS) for pain classification) [33].

Pain management (use of analgesic drugs).

There will be no difference in preoperative or post-operative care between the two groups. All patients will receive 1 dose (1 g) of paracetamol given intravenously at surgery and 2 more, each at 8-hour interval. Additional need for pain management will be noted on the records. The follow-up will be scheduled as follows:1 week (clinical evaluation)4 weeks (clinical evaluation)6 months (clinical evaluation or phone interview)12 months (phone call and eventual clinical evaluation)24 months after surgery (phone call and eventual clinical evaluation)36 months after surgery (phone call and eventual clinical evaluation)

During the follow-up, hernia recurrence (with eventual imaging studies) and post-operative complications will be checked. The following data will be also evaluated, using the licensed Carolinas Comfort Scale (CCS) [34,35]:Pain (during resting, during daily activities, during walking, during exercise):Pain control by use of analgesic drugs (which kind of drug, which dosage)Pain at physical examination

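### Staff who know the tack type record the index-admission secondary outcomes, and no device-blind assessor is tied to them

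*Protocol article*

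**What the plan says.** Four parts of the Protocol article bear on this.

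- **Who records.** *Intervention, preoperative and post-operative management*: "A member of the operating team will note the patients and intervention characteristics in an online database including the following parameters". The list covers patient and hernia features, mesh size, type and number of tacks, operating time and post-operative stay. It is followed by "Post-operative complications during the index admission (according to the Clavien-Dindo classification"), by acute pain on the Visual Numeric Scale (VNS), and by analgesic use.
- **Who is blinded.** *Randomization, allocation concealment, and blinding*: "Patients will be kept blind to the allocation status". For staff, "the operating staff cannot be blinded to allocation but will be instructed not to disclose the allocation status of the participant at any time".
- **The blinded assessor.** The same section says that "post-operative controls will be performed at each center by a physician not directly involved in the study", and of this physician: "He will be kept blind to the particular device used on each patient". The term for these controls is not defined.
- **What the data are for.** *Outcome parameters* makes early surgical complications, stay, comfort and pain the secondary endpoint. The end of *Background* gives the secondary objective as possible superiority of absorbable tacks on these outcomes.

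**The concern.** The investigators openly expect a direction. *Background* rests the non-inferiority design on the idea that absorbable tacks may avoid some complications of metal tacks. *Discussion* treats increased acute and chronic pain as the most clinically relevant drawback of titanium. The outcomes meant to show that advantage in hospital are recorded by people who know which device was used, in the record that also states the device. Telling those people not to disclose allocation protects the patient's blinding. It does nothing for the recorder's own judgement about whether an event counts as a complication and how to grade it.

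At stake is the credibility of the early secondary comparisons. An early difference favouring absorbable tacks could be put down to how events were recorded, and the article offers no safeguard with which to answer that.

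**Working it through.** No figure in the article is in dispute, so the main check is to set the sections side by side.

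**Step 1: are the in-hospital outcomes part of the operating team's list?** Complications, VNS pain and analgesic use stand as separate lines after the list, with no verb and no other person named. The likelier reading is that they continue it. Hospital stay is in the list on any reading.

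**Step 2: is the blinded physician responsible for them?** The post-operative controls may mean only the scheduled follow-up from 1 week to 36 months, or all post-operative assessment including the hospital stay. On the narrow reading, no blinded person covers the index admission. On the broad reading, two different people appear to be responsible for the same data. Either way, nothing says that the blinded physician assesses or grades the index-admission items.

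**Step 3: how exposed is each item?**

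| Item | Judgement by device-aware staff | Exposure |
|---|---|---|
| Clavien-Dindo complications | Detecting and grading the event | Highest |
| Analgesic use, hospital stay | The record is factual, but the decisions behind it may involve judgement; who makes them is not stated | Intermediate |
| VNS pain | Normally rated by the patient, who is blinded | Lowest |
| Recurrence at 3 years (primary) | Checked at follow-up, outside the index admission | Not affected by this point |

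**Step 4: sensitivity for the most exposed item.** The 110 patients per arm come from *Statistical methods*. The rest is assumed: a true complication rate of 20% in both arms, a two-sided 5% test, and under-recording of *d* in the absorbable arm only. With p₁ = 0.20, p₂ = 0.20 − d and p̄ their mean, the chance of a false advantage for absorbable tacks is

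P = Φ[(d − 1.96·SE₀) / SE₁], where SE₀ = √(2p̄(1 − p̄)/110) and SE₁ = √((p₁(1 − p₁) + p₂(1 − p₂))/110).

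| d | Patients of 110 | SE₀ | SE₁ | Argument of Φ | P |
|---|---|---|---|---|---|
| 0 | 0 | – | – | −1.96 | 2.5% |
| 0.02 | 2.2 | 0.0529 | 0.0529 | −1.58 | about 6% |
| 0.05 | 5.5 | 0.0512 | 0.0511 | −0.99 | about 16% |
| 0.08 | 8.8 | 0.0494 | 0.0491 | −0.34 | about 37% |

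The expected number of events per arm is 0.20 × 110 = 22, so the last row supposes that about 9 of 22 events go unrecorded in one arm only. An error in the opposite direction would instead hide a real advantage. The table shows how sensitive the comparison is; it does not estimate what would happen in this trial.

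**The case against.** The strongest reply has four parts.

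1. **No contradiction.** A reader might infer that the blinding section promises blinded assessment and the management section takes it back. The text does not support that. The blinding section itself admits that operating staff are unblinded, and its post-operative controls can naturally mean the follow-up visits. The two sections would then cover different periods and agree. This stands: the defect is a gap in blinded assessment, not a strict contradiction.
2. **Noting is not assessing.** The verb may describe data entry, with someone else grading the events. That is possible, but the article names no other assessor for these items. If transcription is meant, it should say who assesses.
3. **Pain is protected.** Patients are blinded, and *Outcome parameters* names the Carolinas Comfort Scale (CCS), collected at follow-up, for pain and comfort. This stands in large part, and a large pain artefact should not be claimed. It does not remove acute pain altogether. *Discussion* says acute as well as chronic pain will be compared, follow-up starts at 1 week, and the VNS is the only instrument named for acute pain.
4. **An article condenses.** Database roles are often left to the full protocol. Here, however, the article states who records the data, so the point rests on what is written. Complications are also evaluated through readmission and reoperation at 1 to 3 years, which lie outside the index admission. That narrows the exposure to the early outcomes without removing it.

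**Conclusion.** The concern holds as a risk. Followed as written, the plan leaves index-admission complications, hospital stay, analgesic use and, least of all, VNS pain to be recorded by device-aware staff, with no blinded assessor assigned. These data feed secondary comparisons that have a superiority objective, so the change should be made.

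A reader might go further and infer that the secondary comparisons are biased in favour of absorbable tacks. The article does not show that. It shows an opening for differential error whose size and direction are unknown. The range of about 6% to 37% holds only under the assumed 20% rate and the assumed one-sided under-recording.

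The conclusion rests on two readings: that the last three items continue the operating team's list, and that noting includes, or at least does not exclude, assessment.

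**What to change.** - Limit the operating team's entries to patient characteristics, hernia features and operative fields: mesh size, type and number of tacks, and operating time.
- Have the device-blind physician already appointed at each center assess and enter index-admission complications, analgesic use, VNS pain and length of stay, on a separate form that hides tack type.
- As an alternative for complications, let that physician grade them from records in which the device is masked.
- Define post-operative controls so that it is clear whether the index admission is included.

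The cost is a few extra inpatient entries for a physician described as outside the study, and one change to database access. Sample size, treatment and the primary analysis stay as they are.

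One limit remains. Blinded recording does not blind whoever decides on discharge or additional analgesia. The article does not say who that is, so the report should acknowledge this for stay and analgesic use.
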